## 3.2 Definition of Populations to be analysed

The Per-protocol Population:

Includes all participants treated according to the study protocol.

"Intention-to-treat" Population:

Includes all participants consenting and treated at least once. Premature terminations, due to treatment failure, adverse events etc., are included.

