###### Appendices

Appendix 1 Declaration of Helsinki.

Appendix 2 European (CPMP) Guidelines on Good Clinical Practice for Trials on Medicinal Products.

# Introduction

## 1.1 Summary of the Study

Title: A randomized, assessor blinded, clinical trial to confirm the efficacy of a CE marked class I Medical Device formulation in the treatment of head lice

**Chief Investigator:** [name]

**Estimated Study Start:** September 2010

**Estimated Study Finish:** January 2011

**Participants:** One hundred and twenty (120) evaluable participants will be recruited to the study, randomised between three groups and treated with two vairants of the same CE marked product 5% 1,2-octanediol lotions.

**Type:** Children (aged 6 months and over) and adults who, upon inspection, are found to have live head lice.

**Products:** KindaPed AF (5% 1,2-octanediol alcohol free lotion)

KindaPed (5% 1,2-octanediol lotion with 20% alcohol).

**Methods of Application:** KindaPed AF 5% 1,2-octanediol alcohol free lotion (2-2.5 hours) and KindaPed 5% 1,2-octanediol lotion: These products will be applied directly to dry hair. Sufficient product will be applied to saturate the hair and scalp. The product will be left in place for 2 hours (maximum 2.5 hours) before being removed with proprietary shampoo. The product will be reapplied at Day 7.

KindaPed AF 5% 1,2-octanediol alcohol free lotion (8 hours or overnight): This product will be applied directly to dry hair. Sufficient product will be applied to saturate the hair and scalp. The product will be left in place for a minimum of 8 hours, or left on overnight, before being removed with proprietary shampoo. The product will be reapplied at Day 7.

**Study Design:** This is a randomised, assessor blind clinical investigation designed to confirm efficacy in use and obtain further information about routine usage of two variants of the same CE marked class I Medical Device product with the same active principle in the control and elimination of head louse infestation.

Participants will be assessed at Day 0 (recruitment) and then treated. An investigator will apply the treatment. The same treatment will be reapplied on Day 7.

Participants will be assessed for the presence of live head lice on Days 1, 6, 9 and 14 (+/- 1 day). The assessors will be blind to the treatment group. Any lice found at assessments will be taped into the Case Record Form (CRF) for size analysis.

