## Design in Brief

This is a randomised, controlled, assessor blind, study of two variants of the same class I Medical Device product for control of head louse infestation. One hundred and twenty (120) evaluable participants, minimum age 6 months^[[1]](#footnote-1)^, who upon examination are confirmed to have head lice and who fit the selection criteria (see section 2.1.2 and 2.1.3) will be recruited to the study.

At the first visit (Day 0), verbal consent will be obtained to check for the presence of live head lice using a fine-toothed plastic detection comb. After the preliminary assessment, participants can be enrolled to the study, provided they comply with the inclusion/exclusion criteria, and any further questions they may have are fully dealt with.

Participants (or their parents/guardians if they are aged below 16 years) will be asked to give written informed consent and sign a Consent Form before participation in the study. There will be a separate Assent Form for younger children capable of giving written assent. Children too young to give assent can be entered in the study on the consent of a parent/guardian. Assent Forms will be witnessed by the parent/guardian and signed by the Investigator. Consent will be sought for permission to inform the participant’s GP that their patient is taking part in the study. Other infested household members who are unable to participate in the study for any reason, e.g. not being available for the assigned follow up visits, will be offered a standard of care treatment (Hedrin 4% liquid gel) in order to reduce the risk of reinfestation of participants during the course of the study.

The Investigator will assign each participant a study number, this being the next available number allocated to that investigator from a randomised treatment allocation sequence. Participants will be divided between three groups as follows:

Group A: KindaPed AF (5% 1,2-octanediol alcohol free lotion ), applied for 2 hours (maximum 2.5 hours) before washing off using shampoo, with a repeat treatment one week later.

Group B: KindaPed AF (5% 1,2-octanediol alcohol free lotion ), applied for 8 hours (minimum) or overnight before washing off using shampoo, with a repeat treatment one week later.

Group C: KindaPed lotion (5% 1,2-octanediol lotion with 20% alcohol), applied for 2 hours (maximum 2.5 hours) before washing off using shampoo, with a repeat treatment one week later.

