### 2.3.2 Randomisation

The randomised treatment allocation code will be generated using the free online randomisation service provided at <http://www.randomization.com/>. The treatment allocation will be made in 11 balanced blocks of 12 treatments and the Seed number and date of randomisation will be recorded on the randomisation plan.

The treatment allocations will be prepared as sheets bearing the identification of the product to be used and instructions for application of the relevant product. The product identification/instruction sheets will be sealed in opaque envelopes numbered sequentially on the outside with the participant number taken from the randomisation schedule. Each envelope will be enclosed in a CRF prior to use. Each investigator delegated to enrol participants will allocate the numbered CRFs to participants in numerical sequence. However, where two or more investigators, each allocated separate blocks of numbers, enrol participants in parallel the overall numerical sequence will not follow chronologically.

Only after written informed consent has been obtained will the investigator allocate a study number and open the randomisation envelope for that number. The investigating team will keep a second batch of envelopes, and a copy of the randomisation code also in a sealed envelope, in case an adverse event, reaction, or any other emergency circumstance necessitates that the code be broken.

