3. **Hair Characteristics**: Characteristics will be recorded of the participant’s hair:
   1. Length: closely cropped, above ears, ears to shoulders, below shoulders
   2. Thickness: fine, medium, thick
   3. Degree of curl: straight, wavy, slight curl, tight curl
   4. Type: dry, normal, greasy
4. **Head Lice Details**: When the participant was last treated for head lice (an exact date if treated within the previous four weeks), the treatment that was used and the outcome (success or failure). The severity of the current louse infestation will be assessed using the following scale:
   1. Light infestation: single louse found only after 5-6 combs of the hair
   2. Moderate infestation: single louse found on the first comb of the hair
   3. Heavy infestation: more than one louse found on the first comb of the hair
5. **Medication Current at Entry**: Any medication being taken along with the date the medication started the total dose and the reason for the medication.
6. **Medical History**: Medical history and any current illnesses will be recorded.
7. **Inclusion/Exclusion Criteria**: Confirmation that the participant meets the inclusion/exclusion criteria for entry into the study.

Randomisation:

The Investigator will carry a block of sequential numbered envelopes, which correspond to the randomisation numbers on the CRFs. Each envelope will contain a randomised treatment allocation. After consent has been received, the next sequential numbered envelope will be opened and the specified treatment allocated.

Treatment:

A member of the study team will apply the treatment to the participant and the participant number and participant initials will be added to the label of the bottle used. Any unused product will be retained and returned to so that the weight can be recorded and the amount of product used calculated.

The products will be applied in the following way:

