**KindaPed AF (5% 1,2-octanediol alcohol free lotion) 2-2.5 hours** will be applied directly to dry hair. Sufficient product will be applied to wet all the hair and scalp. More than one bottle can be used if required. The product will be left in place for 2 hours, however for practical purposes and convenience of the participants a small flexibility has been included in the treatment time so that the product may remain on the hair for up to 2.5 hours. The product will then be washed off using non-medicated shampoo. The hair will then be rinsed with water. Hair can be dried in the usual way following hair washing after treatment.

**KindaPed AF (5% 1,2-octanediol alcohol free lotion) 8 hours or overnight** will be applied directly to dry hair. Sufficient product will be applied to wet all the hair and scalp. More than one bottle can be used if required. The product will be left in place for at least 8 hours, if applied early enough during the day, but if applied late it will be left on overnight. The product will then be washed off using non-medicated shampoo. The hair will then be rinsed with water. Hair can be dried in the usual way following hair washing after treatment.

**KindaPed lotion (5% 1,2-octanediol with 20% alcohol)** will be applied directly to dry hair. Sufficient product will be applied to wet all the hair and scalp. More than one bottle can be used if required. The product will be left in place for 2 hours, however for practical purposes and convenience of the participants as small flexibility has been included in the treatment time so that the product may remain on the hair for up to 2.5 hours. The product will then be washed off using non-medicated shampoo. The hair will then be rinsed with water. Hair can be dried in the usual way following hair washing after treatment.

In all cases the participants will be reminded that a second treatment will be applied on Day 7.

Any household members who have lice but are unable to participate in the study for any reason will be offered a standard of care treatment (Hedrin 4% liquid gel) in order to reduce the risk of reinfestation of participants during the course of the study.

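### The set labelled intention-to-treat holds only people treated at least once, so anyone left untreated after the envelope is opened drops out of the primary analysis

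*Protocol*

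**What the plan says.** Section 3.2 of the protocol says of the intention-to-treat population: "Includes all participants consenting and treated at least once". It adds: "Premature terminations, due to treatment failure, adverse events etc., are included". The per-protocol population, in the same section, is limited to those treated according to the protocol. Section 3.4 makes the intention-to-treat set the one for the primary endpoint and plans analyses in both sets.

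The order of events on Day 0 is fixed in two places. Section 2.3.2 says: "Only after written informed consent has been obtained will the investigator allocate a study number and open the randomisation envelope for that number". Section 2.3.3.2 says: "After consent has been received, the next sequential numbered envelope will be opened and the specified treatment allocated". Application of the product follows.

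The envelope is informative. Section 2.3.2 says: "The treatment allocations will be prepared as sheets bearing the identification of the product to be used and instructions for application of the relevant product". Blinding is claimed for the assessors only; section 1.1 states: "The assessors will be blind to the treatment group".

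The regimens differ in contact time. Group B's product is "applied for 8 hours (minimum) or overnight before washing off using shampoo" (Design in Brief), and section 2.3.3.2 adds: "The product will be left in place for at least 8 hours, if applied early enough during the day", with overnight use otherwise. Groups A and C both use 2 hours, with 2.5 hours as the maximum.

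**The concern.** An intention-to-treat set protects the randomised comparison because membership is settled at randomisation. Here membership is settled later, by whether product was applied. A set of people treated at least once is usually defended on the ground that neither the participant nor the treating staff know the allocation, so not being treated cannot depend on it. That defence is not available: the investigator who opens the envelope learns the product and the contact time before the first application, and nobody but the assessors is blind.

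A participant who will not accept the allocated regimen, or whom the investigator does not go on to treat, has consented and been randomised but belongs to neither analysis population. If this happened more often in one arm, that arm's cure rate would be calculated on a more willing subset. Contact time is the most visible difference between arms, and the Day 14 questionnaire asks how convenient it was, so the protocol itself treats it as an acceptability issue. At stake is the cure rate for Group B and its difference from the other groups, together with the 95% confidence limits and the judgement of essential similarity in section 3.4.

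**Working it through.** **1. Who is kept and who is lost**

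- Randomised, never treated: fails the treated-at-least-once condition in section 3.2, is not per-protocol, and is in no defined set.
- Product applied once, then washed off early: treated, so kept.
- Product applied once, then refuses Day 7 or drops out: kept, and premature terminations are named expressly.
- Kept, but with no Day 9 or Day 14 assessment: the treatment outcome algorithm in section 3.1.2 puts the person in the combined licidal and ovicidal failure category, so not cured.

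The gap is therefore confined to people lost between the opening of the envelope and the first application.

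**2. The protocol's own numbers**

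- Evaluable participants: 120 in three groups, 120 / 3 = 40 per group (sections 2.1.1 and 3.4).
- Allocation schedule: 11 blocks × 12 = 132, and 132 / 3 = 44 per group if all are used (section 2.3.2).
- Spare allocations: 132 − 120 = 12, and 12 / 132 = 9.1%.

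The sums agree. Because the target is counted in evaluable participants and there are 12 spare allocations, a group could reach 40 even if some allocations were opened and not followed by treatment. The 40 per group itself cannot be derived from the protocol, which gives no significance level, power, cure rate or dropout rate. This point does not depend on it.

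**3. Size of the effect**

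Let n be the number randomised to an arm, k the number never treated, and p the cure rate among the treated.

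- Cure rate in the treated-only set: p
- Cure rate in all randomised, untreated counted as not cured: p(n − k)/n
- Difference: p × k/n

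The protocol gives neither p nor k. Both are assumed, with p from 70% to 90% and n = 44:

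| k untreated in one arm | p = 70% | p = 90% |
|---|---|---|
| 0 | 0 | 0 |
| 1 | 1.6 points | 2.0 points |
| 2 | 3.2 points | 4.1 points |
| 4 | 6.4 points | 8.2 points |
| 6 | 9.5 points | 12.3 points |

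As one worked case, with p = 80% and k = 4, the all-randomised rate is 0.80 × 40/44 = 72.7%, a difference of 7.3 points. With n = 40 instead, k = 4 gives 7.0 to 9.0 points.

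**4. Scale**

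With 40 per arm, two-sided 5% significance and 80% power (both assumed), the smallest detectable fall from a cure rate of 70 to 90% is about 26 to 31 points. One or two omitted people would shift an estimate and its interval by a few points but would seldom change a test result.

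**The case against.** The strongest defence is that the window is short and well guarded. Families have the information booklet for at least 24 hours (section 2.3.3.1), are asked again before signing whether they understand the requirements and still wish to enter, and have the product applied by staff as part of the Day 0 procedures (section 2.3.3.2). The commoner consequences of a long contact time, namely early removal, refusal of the second treatment and drop-out, all come after a first application and are already kept. The final report must give numbers entered, completed and withdrawn, with an explanation of each withdrawal (section 4.6), so an all-randomised count could probably be rebuilt. All of this stands. It limits how many people are likely to be lost, but it does not put them back in the primary set.

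A reader might infer more than the protocol supports:

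- That families watch the envelope being opened and refuse the overnight regimen. The text does not say who is present, and it gives no refusal rate for any group.
- That the randomised comparison as a whole is broken. Groups A and C share the same contact time, so the contact-time mechanism does not touch the comparison of the two formulations at 2 to 2.5 hours. Their alcohol content differs and is also revealed by the envelope, but the protocol gives no ground for expecting refusals on that account. Section 3.4 also describes the primary test as a comparison with groups from previous studies, which is not randomised in any case.
- That silence about analysing people in their allocated group is itself an error. That detail may properly be left to the statistical analysis plan.

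**Conclusion.** The point holds as one of definition, with a possible but unquantified bias. The protocol states the rule outright, so this is not a detail awaiting the analysis plan: the primary set is conditioned on an event after randomisation, the allocation is known by then, and nothing elsewhere restores the people excluded. The exposure lies mainly in B against A and B against C.

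Each omitted person raises the arm's cure rate by about 1.6 to 2.0 points. This assumes 70 to 90% cure among the treated, 44 randomised per arm, and that untreated people count as not cured. The number omitted is unknown and may be zero, in which case the results are the same under either definition. It would be wrong to say that the cure rate for Group B will be inflated; the protocol only permits it. This is a worthwhile correction of modest weight.

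**What to change.** Replace the definition in section 3.2 with one sentence: the intention-to-treat population is all randomised participants, analysed in the group allocated, whether or not treated, with untreated participants classed as not cured. This extends the rule already in the section 3.1.2 algorithm for missing Day 9 or Day 14 data, so no new outcome category is needed. Report the number randomised but not treated, by arm. Keep the treated-at-least-once set under its proper name, as the safety or modified intention-to-treat population.

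The cost is one sentence and one line in the participant flow. Two small downsides follow. The primary cure rate may come out slightly lower. And if the earlier studies used in the section 3.4 comparison were analysed on a treated-at-least-once basis, which the protocol does not say, results in that set should be shown alongside so that like is compared with like.

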## 3.3 Proposed Primary and Secondary Analyses

1. To compare efficacy of KindaPed AF (5% 1,2-octanediol alcohol free lotion) with KindaPed (5% octanediol lotion with 20% alcohol) for elimination of infestation by head lice.
2. To compare KindaPed AF (5% 1,2-octanediol alcohol free lotion) with KindaPed (5% octanediol lotion with 20% alcohol) with regard to prevention of louse egg hatching (ovicidal action) by monitoring the presence/absence of juvenile stages of lice following the first and second treatments.
3. To compare KindaPed AF (5% 1,2-octanediol alcohol free lotion) with KindaPed (5% octanediol lotion with 20% alcohol) To investigate 5% 1,2-octanediol alcohol free lotion with regard to participant acceptability.

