## 1.3 Aims (Objectives)

1. To compare efficacy of KindaPed AF (5% 1,2-octanediol alcohol free lotion ) with KindaPed (5% octanediol lotion with 20% alcohol) for elimination of infestation with head lice.
2. To compare KindaPed AF (5% 1,2-octanediol alcohol free lotion ) with KindaPed (5% octanediol lotion with 20% alcohol) with regard to prevention of louse egg hatching (ovicidal action) by monitoring the presence/absence of juvenile stages of lice following the first and second treatments.
3. To compare KindaPed AF (5% 1,2-octanediol alcohol free lotion ) with KindaPed (5% octanediol lotion with 20% alcohol) To investigate 5% 1,2-octanediol alcohol free lotion foam with regard to safety and participant acceptability.

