## 3.4 Statistical Methods

Sample Size Determination:

The study has been designed to confirm that KindaPed AF (5% 1,2-octanediol alcohol free lotion) has an essentially similar efficacy comparable to that of KindaPed lotion (5% 1,2-octanediol with 20% alcohol). It is not designed as a full equivalence study but is designed to be able to identify any significant differences between the treatments in pair wise comparisons.

This study is based upon the same sample size as that used in four previous studies of head louse treatments conducted on behalf of Thornton & Ross Ltd (CTMK06, CTMK08, CTMK09, and CTMK10) for basic comparative purposes and is estimated to provide adequate data for demonstration of effect. The actual sample size of 40 per group makes allowance for dropout. Comparison of the results from this study can be made with the results from those studies with respect to similarities of population demographics, and with previous studies of 1,2-octandiol lotion (CTEP01 and CTEP02) with respect to efficacy outcome and acceptability.

Interim analysis

It is proposed to conduct an interim analysis of treatment outcome only after enrolment and completion of sixty (60) participants (approximately 20 in each group). This analysis will be conducted blind of treatment allocation using outcome data entered into a spreadsheet which would then be overlaid with treatment allocation identified only as “a”, “b”, or “c”. This will enable the Sponsor to identify whether one treatment is performing exceptionally well or exceptionally poorly and allow them to make a decision in good time whether they wish to extend or to curtail any aspect of the study. The results of this analysis will be conveyed to the Sponsor in narrative form only.

Analytical Methods:

The primary endpoint is the frequency of cure tested using the "intention-to-treat" population in comparison with the body of data obtained during previous studies using overnight or 2-2.5 hour application times for the product. Secondary endpoints will be the frequency of ovicidal failure and of reinfestation and the numbers of lice seen at the different assessment times. Other endpoints will be the safety of the product and participant acceptance.

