Analyses will be conducted based on both the "intention-to-treat" and the "per-protocol" populations. The study group will be compared with study groups from previous studies in which participants were treated using an 8 hour/overnight treatment or a 2-2.5 hour treatment on baseline characteristics, safety, acceptability, and efficacy using Fisher's exact test for yes/no variables and the Mann-Whitney U test for ranked variables. Where analysis shows important differences in baseline characteristics, chi squared and rank tests stratified for these characteristics may also be conducted. 95% confidence limits will be presented for the difference between this study group and previous groups in the primary endpoint.

These analyses will be used to determine whether the study provides evidence of essential similarity between KindaPed AF (5% 1,2-octanediol alcohol free lotion) and KindaPed (5% 1,2-octanediol lotion) in the elimination of infestation.

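### Safety of KindaPed AF is to be tested only against groups from previous studies, although group C is a concurrent randomised KindaPed arm with group A's application time, and section 3.3 item 3 drops safety from aim 3

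*Protocol*

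**What the plan says.** **Aim.** Section 1.3, item 3, opens as a comparison of KindaPed AF with KindaPed and ends "To investigate 5% 1,2-octanediol alcohol free lotion foam with regard to safety and participant acceptability".

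**Planned analysis.** Section 3.3, item 3, has the same opening but ends "To investigate 5% 1,2-octanediol alcohol free lotion with regard to participant acceptability". Safety is absent.

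**Test.** Under Analytical Methods, section 3.4 states: "The study group will be compared with study groups from previous studies in which participants were treated using" an 8 hour/overnight or a 2-2.5 hour application, "on baseline characteristics, safety, acceptability, and efficacy using" Fisher's exact test for yes/no variables and the Mann-Whitney U test for ranked ones. The next interval statement is "95% confidence limits will be presented for the difference between this study group and previous groups in the primary endpoint". It concerns efficacy only and is also against earlier groups.

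**Between-arm intent.** Under Sample Size Determination, section 3.4 says that the trial "is designed to be able to identify any significant differences between the treatments in pair wise comparisons". The same subsection lists what the earlier octanediol studies (CTEP01 and CTEP02) are to be used for: efficacy and acceptability. Safety is not in that list.

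**Design.** Design in Brief defines "Group C: KindaPed lotion (5% 1,2-octanediol lotion with 20% alcohol), applied for 2 hours (maximum 2.5 hours) before washing off using shampoo", with a repeat one week later. Group A has the same schedule with KindaPed AF. Section 2.3.1 randomises each participant to one of the three groups, and sections 2.3.3.3 and 2.3.5 record adverse events in all of them.

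**The concern.** The reason for making the alcohol-free product is tolerability. Section 1.2 attributes a number of mild reactions on excoriated skin to the isopropanol in KindaPed, and expects KindaPed AF not to irritate. Whether AF is better tolerated than KindaPed is therefore a question that the trial should answer with its best evidence.

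The best evidence is the randomised contrast of A with C: same period, same visits, same CRF, same application time, different formulation. Section 3.4 instead names groups from previous studies. A difference found that way could come from the formulation, the calendar period, the people enrolled, or how events were asked about and written down. The stratified tests that section 3.4 allows deal only with baseline characteristics, so they cannot correct for a difference in event recording. Followed as written, aim 3 would be answered by the weaker comparison while the data for the stronger one are collected anyway.

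**Working it through.** **Step 1. Set the statements side by side.**

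| Place | Safety named? | Comparator for safety |
|---|---|---|
| 1.3 item 3 | yes | KindaPed |
| 3.1.1 and 3.1.2 | yes (in 3.1.2 among the secondary endpoints) | none stated |
| 3.3 item 3 | no | – |
| 3.4, sample size, pairwise statement | no (follows a sentence on efficacy) | – |
| 3.4, sample size, use of earlier octanediol studies | no | – |
| 3.4, list of other endpoints | yes | none stated |
| 3.4, comparison sentence | yes, with a test | previous studies |
| 3.4, confidence limits | no (primary endpoint only) | – |

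Only one row gives safety a test, and its comparator is not randomised. It does not fit the pairwise intent, and the list of uses for the earlier octanediol studies does not support it.

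**Step 2. What A v C can show.** The protocol gives no adverse-event rate, significance level or power, so there is no figure to reproduce. The only input is 120/3 = 40 per group. A two-sided 0.05 level is assumed.

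*Fisher thresholds, 40 v 40.* With no events in A and k in C, the two-sided p is 2 × C(40,k)/C(80,k).
- k = 5: 2 × 658,008/24,040,016 = 0.055.
- k = 6: 2 × 3,838,380/300,500,200 = 0.0255.

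So 0 v 6 is the first significant split. Full enumeration gives the others:

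| A v C, participants with an event | p | Gap in points |
|---|---|---|
| 0 v 6 | 0.0255 | 15 |
| 1 v 8 | 0.0289 | 17.5 |
| 2 v 9 | 0.0476 | 17.5 |
| 3 v 11 | 0.0367 | 20 |
| 4 v 12 | 0.0482 | 20 |

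*Interval width (Newcombe, built from Wilson limits).* For 2/40 v 8/40 the Wilson limits are 0.014 to 0.165 and 0.105 to 0.348, and the difference is −0.15.
- Lower limit: −0.15 − √[(0.05 − 0.014)² + (0.348 − 0.20)²] ≈ −0.302.
- Upper limit: −0.15 + √[(0.165 − 0.05)² + (0.20 − 0.105)²] ≈ −0.001.
- Fisher p for these counts is 0.087.

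By the same method, 2/40 v 2/40 gives 0 (−12.1 to +12.1 points) and 2/40 v 4/40 gives −5 (−18.5 to +8.0 points).

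*Power.* This is the sum of Bin(a; 40, pA) × Bin(c; 40, pC) over all pairs (a, c) with Fisher p ≤ 0.05. All rates are assumed.

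| AF rate | KindaPed rate | Power |
|---|---|---|
| 0% | 10% | 21% |
| 0% | 15% | 57% |
| 0% | 20% | 84% |
| 5% | 10% | 4% |
| 5% | 15% | 18% |
| 5% | 20% | 41% |
| 5% | 25% | 65% |
| 5% | 30% | 82% |
| 10% | 20% | 16% |
| 10% | 30% | 53% |

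**The case against.** **The text is muddled rather than firm.** Section 3.4 speaks of one study group in a three-arm trial, the pairwise statement shows that between-arm comparison was intended, and nothing forbids tabulating adverse events by arm. That is fair. But the pairwise statement names neither safety nor a test, and the sentence that does both names previous studies. A SAP that followed that sentence would carry the fault forward, and one that did not would contradict the protocol. This is a rule fixed badly, not a detail left open.

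**The harm is not shown.** This stands. A reader might infer that the historical comparison would mislead by a known amount, but the protocol gives nothing from which to compute it. As an illustration with every rate assumed, take two groups of 40 and a true rate of 5% with both products. If the earlier group was recorded at 5%, 7.5%, 10% or 15%, Fisher's test would wrongly find a difference 0.4%, 1.4%, 4.3% or 18% of the time. The effect is small unless recording differs by about 10 points, and nothing in the protocol shows that it does.

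**Any-event counts do not match the irritation rationale.** This also stands. All events are recorded whether or not they are thought related, so unrelated ones would dilute an irritation effect. Irritation events need their own line. The listed baseline items contain no explicit entry for excoriation, so a subgroup on that basis may not be available.

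**The gain is limited.** Power is modest at 40 per group. That argues for an estimate with its interval and for restraint in reading it, not for a non-randomised comparator.

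**Conclusion.** The point holds. Safety is part of aim 3, is missing from section 3.3 item 3, and is given a non-randomised comparator in section 3.4 although a concurrent randomised one exists. This should be corrected. It does not undermine the trial, since safety is not the primary endpoint and the data needed are collected regardless.

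Two stronger readings are tempting and are not supported. A reader might infer that safety goes unanalysed. It does not: sections 3.1.1, 3.1.2 and 3.4 all keep it. A reader might also infer that amending the comparison sentence would repair the efficacy comparator too. It would not, because efficacy is also tied to previous studies in the primary-endpoint sentence and in the confidence-limits sentence of section 3.4.

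The thresholds and intervals rest on 40 per group, and the thresholds and power on a two-sided 0.05 level. Power rests further on assumed event rates. The direction and size of any cross-study bias are unknown.

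**What to change.** 1. In section 3.3 item 3, restore *safety and* before participant acceptability.

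2. In section 3.4, take safety out of the comparison with previous studies and state the randomised contrast. For example: *Among all treated participants, the proportion with any adverse event and, separately, the proportion with a scalp or skin irritation event will be compared between the randomised groups. A v C is the main contrast and B v C is supportive. Each will be given as a risk difference with 95% CI and Fisher's exact test. Results of earlier studies will be shown as descriptive context only.* The population is the intention-to-treat one of section 3.2: "Includes all participants consenting and treated at least once".

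3. This settles safety only. If the efficacy comparator is to be corrected as well, the efficacy part of the comparison sentence, the primary-endpoint sentence and the confidence-limits sentence in section 3.4 must also change.

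The cost is two words in section 3.3 and one amended sentence in section 3.4, with no new data, visits or participants. B v C differs in application time as well as formulation, which is why it is only supportive. Only the assessors are stated to be blind, so participants' reports may be coloured by knowing the product. With 40 per group only large differences can be shown, and the report should say that a non-significant result is not evidence of equal safety.
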